### Statistical analysis

At the conclusion of the study, intention to treat analyses will be done. Missing values will be replaced by using the Last Observation Carried Forward (LOCF) method. Additional sensitivity analyses using further imputation methods will also be done. For the primary analysis, both experimental treatment groups (FPT and CBT) will be compared with the TAU control group. The primary outcome – BMI at T2 – will be analysed using a mixed modelling approach. The grand mean, the treatment effects, and the stratification variable will be designed as fixed effects. The centre effect will be modelled as a random effect. The baseline BMI is entered as covariate in the model. The model can be written as:

where *Y*_*ijkl *_denotes the BMI at T2 on the *l*th patient  on treatment *i *(*i *= 1,2,3) in stratum *j *(*j *= 1,2) in centre *k *(*k *= 1,...10), μ denotes the overall mean, *τ*_*i *_denotes the effect of the *i*th treatment, *α*_*j *_denotes the effect of the *j*th stratum, *ζ*_*k *_denotes the random effect of the *k*th centre (*ζ*_*j *_~N(0, )), β denotes the baseline covariate effect, *X*_*l *_denotes the baseline BMI on the *l*th patient, and *ε*_*ijkl *_denotes a residual error with *ε*_*ijkl *_~ N(0, ). The parameters of interest in this confirmatory analysis are the mean of the control group *μ *+ *τ*_1 _and the contrasts of the means *τ*_2 _- *τ*_1 _and *τ*_3 _- *τ*_1 _(that indicate the treatment effects of FPT and CBT).

The secondary outcome measures will also be analysed using mixed models. No interim or subgroup analyses are planned.

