### Outcomes

The primary outcome measure is the body mass index (BMI) at the end of the treatment (10 months after randomization). Secondary outcome measures are: the Morgan-Russell-criteria [17,18]; general axis I psychopathology (SCID I) [19]; eating disorder specific psychopathology (SIAB-Ex; Eating Disorder Inventory-2) [20,21]; severity of depressive comorbidity (PHQ-9) [22]; and quality of life according to the SF-36 [23]. The therapeutic alliance is assessed by the Helping Alliance Questionnaire (HAQ) [24]. Table 2 shows the assessments and outcome measurements at the different time points in the study.

**Table 2 T2:** Assessment of secondary outcome measures within the ANTOP study

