### Sample size calculation

Estimates of a clinically relevant effect size were derived from two randomized controlled studies that evaluated the effects of FPT and CBT in outpatients with AN [10,25]. Based on these findings, it was assumed that the different interventions would result in an improvement of 1.0 BMI-points compared to the TAU-group, with a pooled standard deviation of 1.7 BMI-points (effect size = 0.59). As the hypothesis for the primary efficacy endpoint comprises two statistical tests, namely FPT vs. TAU and CBT vs. TAU, the nominal α-level was set to 2.5% (two-sided) in order to restrict the Type 1 error level to 5%. Calculations were done to detect an effect size of 0.59 for a comparison power of 80%. Using a two-sample t-test, a sample size of 55 patients per treatment arm was required, resulting in a total sample size of n = 3*55 = 165. Considering a non-compliance and loss to follow up rate of 30% in total, a minimum of 237 patients must be included in the study.

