### Medical complications

If, over the course of a two-week measurement period, a patient of an intervention group (CBT, FPT) has a BMI < 14, the outpatient treatment is interrupted and the patient is hospitalized. If the inpatient treatment leads to an improvement within four weeks (BMI ≥ 14), the outpatient treatment is resumed; if there is no improvement, the patient is withdrawn from the intervention treatment. Patients of the TAU-condition are advised to see their general practitioner (GP) on a regular monthly basis to monitor weight and possible medical complications. The study staff is in contact with the GPs to arrange more intensive treatment for the patient if necessary. Moreover, a control of relevant blood parameters is also part of the diagnostic measurement points (T0 – T3).

In the event of medical complications such as malnutrition or the manifestation of a severe psychiatric disorder, short-term hospitalization should be considered. For further clinical decisions, the guidelines of the American Psychiatric Association 2006  as well as the recommendations of J. Treasure  should be considered.

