## Discussion

The ANTOP study aims to provide new evidence about the efficacy of two different therapy approaches in the outpatient treatment of anorexia nervosa: focal psychodynamic therapy and cognitive-behavioural therapy. The design of the study overcomes the disadvantages of previous studies in that it provides a randomized controlled design, a large sample size, adequate inclusion criteria, an adequate treatment protocol, and a clear separation of intervention conditions.

This is the first multi-centre trial to include a sample size of adults with AN that is large enough to detect a reasonable effect size. The assumed drop-out rate of 30% is similar to the drop-out rates of previous smaller trials. As the assumed drop-out rate is quite high, special attention must be given to the method of missing data imputation in the data analysis. The ANTOP study is further distinguished from previous studies in that an adequate definition of inclusion criteria has been formulated. For instance, McIntosh et al. [9] included patients with an average BMI of 17.3; this made it difficult to generalize the results to patients with AN. In the ANTOP study, the inclusion criteria of having AN (or subsyndromal AN) and a BMI between 15.0 and 18.5 kg/m^2 ^ensure that the sample of patients included in the study is representative. Furthermore, in contrast to the study of McIntosh et al. [9], the various treatments are provided by different therapists to avoid contamination.

Another noteworthy aspect of the study is the choice of treatment-as-usual as a control condition. This was done for several reasons. Studies that imposed a wait-list control condition in AN patients reported drop-out rates of up to 70% [26]. In another trial, a control arm that used dietary advice had a 73% overall treatment failure rate [25]. Due to the ethical problem of denying active treatment to AN patients, and considering the fact that the health care system in Germany enables every AN patient to get both in- and outpatient psychotherapy, it appeared to be advisable to choose TAU as a control condition. With this choice, the study faces the problem that therapeutic interventions in the TAU-condition could be quite heterogeneous. In order to give consideration to this heterogeneity, the treatment dosage and approaches used in the TAU-condition is documented in detail.

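### LOCF is the primary method for missing BMI at T2, which can shrink a true effect or create a false one and overstates precision about T2 BMI

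*Protocol article*

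**What the plan says.** The Statistical analysis section of the protocol article plans intention-to-treat analyses and fixes the handling of missing data: "Missing values will be replaced by using the Last Observation Carried Forward (LOCF) method". It adds sensitivity analyses with other imputation methods, none of them named. The completed data then enter a mixed model for BMI at T2 with treatment and stratum as fixed effects, centre as a random effect and baseline BMI as covariate. The FPT–TAU and CBT–TAU contrasts from that model are the confirmatory results.

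The Sample size calculation section assumes "an improvement of 1.0 BMI-points compared to the TAU-group", a standard deviation of 1.7, a two-sided level of 2.5% per comparison and 80% power. It inflates the sample for 30% non-compliance and loss to follow-up together. The Abstract and Discussion call the same 30% drop-out, and the Discussion draws the consequence: "As the assumed drop-out rate is quite high, special attention must be given to the method of missing data imputation in the data analysis".

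The Medical complications section mentions weighing between visits in two places. For the intervention arms, its hospitalization rule applies when "over the course of a two-week measurement period, a patient of an intervention group (CBT, FPT) has a BMI < 14". For the control arm, "Patients of the TAU-condition are advised to see their general practitioner (GP) on a regular monthly basis to monitor weight". Neither sentence says that these weights are used to fill in T2.

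**The concern.** LOCF replaces a missing T2 BMI with an earlier BMI, as if weight stopped changing on the day of drop-out. The trial assumes the opposite: its sample size rests on BMI diverging between arms over 10 months, and its safety rules provide for severe weight loss. A carried value therefore estimates BMI at some earlier time, not at T2, which is the endpoint named under Outcomes.

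Two errors can follow in the confirmatory contrasts. If the arms lose similar proportions, a real difference is diluted, because drop-outs keep only part of their change. If they lose different proportions and weight generally rises, the arm with fewer drop-outs looks better without any treatment effect. The sign depends on which arm loses more, so LOCF cannot be defended as conservative. In addition, every carried value enters the model as a T2 observation, so the interval conveys more knowledge of T2 BMI than the trial has. The promised sensitivity analyses do not change which estimate decides the hypotheses.

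**Working it through.** **The protocol's own figure.** With d = 0.59, level 2.5% two-sided and power 80%: n = 2(2.2414 + 0.8416)² / 0.59² = 54.6, so 55 per arm. Then 55 / 0.7 = 78.6, so 79 per arm, and 3 × 79 = 237. This reproduces by the normal approximation. The exact t-test needs about 56 to 57 per arm and has power 0.79 at 55, a negligible difference.

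**Inputs.** From the protocol: difference 1.0, SD 1.7, 30%, level 2.5% per comparison, 79 per arm. Assumed, because the text does not give them: T1 at month 5; linear change in BMI; drop-out uniform in time and unrelated to outcome; mean gains of 1.5 (intervention) and 0.5 (TAU) when the true difference is 1.0, and 1.0 in both when it is zero; baseline SD 1.0; SD of change 1.3 (T2 SD about 1.67).

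**Formula, visits at T0, T1 and T2 in every arm.** Half the drop-outs leave before T1 and carry a gain of 0; half leave after it and carry 0.5G. The mean carried gain is 0.25G, so with drop-out proportion d

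LOCF arm mean gain = (1 − d)G + d × 0.25G = G(1 − 0.75d).

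**Equal drop-out, true difference 1.0.** The estimate is 1.0 × (1 − 0.75d): 0.775 at d = 0.30, 0.85 at 0.20 and 0.925 at 0.10.

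**No true difference, unequal drop-out.** Bias = 0.75 × (d_TAU − d_intervention) × G. At 20% against 40% with G = 1.0: 0.85 − 0.70 = +0.15. With the proportions reversed it is −0.15. With the LOCF standard error of 0.196, the rejection rate is P(Z > 2.241 − 0.15/0.196) + P(Z < −2.241 − 0.15/0.196) = 0.071. The bias scales with the assumed common gain: G = 0.5 gives +0.075 and 3.6%; G = 1.5 gives +0.225 and 13.7%.

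**Simulation** (ANCOVA on baseline BMI, one intervention arm against TAU, 79 per arm, 3,000 runs per scenario):

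| Scenario | LOCF estimate | Rejection rate |
|---|---|---|
| True 1.0, 30%/30%, same visits | 0.78 | 0.955 |
| True 1.0, 30%/30%, two-weekly vs monthly weights | 0.85 | 0.978 |
| True 1.0, 30%/30%, two-weekly vs T1 only | 0.88 | 0.986 |
| No effect, 30%/30%, same visits | 0.00 | 0.024 |
| No effect, 30%/30%, two-weekly vs monthly | +0.01 | 0.021 |
| No effect, 30%/30%, two-weekly vs T1 only | +0.07 | 0.033 |
| No effect, 30%/30%, two-weekly vs baseline only | +0.14 | 0.073 |
| No effect, 20%/40%, same visits | +0.15 | 0.070 |
| No effect, 20%/40%, two-weekly vs baseline only | +0.30 | 0.232 |

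The first schedule named is the intervention arm, the second TAU; drop-out is in the same order. The simulation agrees with the formula.

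**Precision.** In the scenarios with 30% missing in each arm, the LOCF model standard error is 0.196 to 0.201; analysing only the observed T2 values gives 0.26. Part of the gap is the count (79 against about 55 per arm): 0.26 × √0.7 = 0.22. LOCF falls below even that, because values carried from early visits have had less time to vary.

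**The case against.** **The 30% is not missing T2 data.** It combines non-compliance with loss to follow-up, and the legend to Figure 1 ties T2 to 10 months after inclusion, so a patient who stops therapy can still be measured. This stands: 30% is an upper figure, and attenuation is milder below it, as the values for 20% and 10% show.

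**Arm-specific weighing.** A reader might infer that intervention drop-outs carry a recent weight and TAU drop-outs an old one. The documents do not support this: the two-week period and the advised GP visits belong to the safety text, and nothing says those weights feed LOCF. Two-weekly against monthly weights adds only +0.01. Schedules matter more only if TAU patients have few or no interim weights and the intervention weights are used.

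**Standard errors.** A reader might infer that they are too small in the ordinary sense. They are not: the model standard error (0.196 to 0.201) matches the spread of the LOCF estimates (0.195 to 0.199). Excess type I error comes from bias. The overstated precision concerns T2 BMI as the target.

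**BMI below 14.** A reader might infer that these low values are carried forward. The rule withdraws patients from the intervention treatment, not from follow-up.

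**Imbalance is assumed.** The protocol gives one overall rate, and at equal drop-out with common visits LOCF keeps its type I error (0.024). Power does not suffer either (0.955 against 0.941 from observed values only). Both stand: under equal loss the damage is to the size of the estimate.

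**LOCF is not always the worse choice.** When drop-out was made likelier in patients with a poorer weight course, LOCF at 20%/40% with no true effect gave +0.06 and 2.9% rejection, while analysing observed T2 values only gave −0.26 and 14.9%. This stands against a completers' analysis, which is not what is proposed here. It also shows that a missing-at-random analysis needs a companion that departs from that assumption.

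**The protocol promises sensitivity analyses.** It does, and naming them may be left to a document not shown. The choice of primary method is nevertheless stated here.

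**Conclusion.** The point holds as a should-fix item. LOCF is fixed as the primary method although the protocol itself flags high drop-out, and its assumption of constant BMI conflicts with the premise of the trial. With 30% missing in each arm, a true difference of 1.0 is estimated at about 0.78 to 0.88. With no true difference, an assumed 20%/40% split and a common gain of 1.0 give about +0.15 and a type I error of about 7% against 2.5%, with identical visits in all arms. Reversing the split reverses the sign.

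These sizes rest on linear change, uniform drop-out unrelated to outcome and T1 at month 5. The false-positive figure also rests on an imbalance that the documents neither predict nor exclude. Any effect of different weighing schedules is conditional on those weights feeding LOCF, which the protocol does not say.

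**What to change.** Make the primary analysis a likelihood-based repeated-measures mixed model on BMI at the visits common to all arms, with treatment-by-visit, baseline BMI-by-visit, stratum and random centre, and test the two T2 contrasts at the stated level. Multiple imputation followed by the model already specified is an acceptable alternative. Confirm that BMI is recorded at T1 in every arm, since the gain over analysing observed T2 values comes from that visit.

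Move LOCF to the sensitivity analyses, and name at least one that departs from missing-at-random: control-based (TAU-referenced) or delta-adjusted imputation.

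The cost is a short change to the analysis wording before unblinding, a little more analysis work and slightly wider confidence intervals. No new data are needed, and N = 237 stands.

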### Safety aspects

In AN patients, food restriction can lead to life threatening starvation that requires inpatient medical monitoring and treatment. As food restriction and severe weight loss are central to the psychopathology of AN, an intermittent inpatient treatment up to four weeks is not considered a Serious Adverse Event (SAE). All other fatal or life-threatening events are defined as SAE. SAEs have to be reported immediately to the principal investigator and the central ethics committee. All adverse events are documented and reported to the principal investigator. An Independent Safety Monitoring Board was implemented at the outset.

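### The SAE definition omits hospital admission, exempts stays up to four weeks in wording wider than its weight-loss reason, and leaves longer stays outside unless fatal or life-threatening

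*Protocol article*

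**What the plan says.** The SAE rule is in the Safety aspects section of the protocol article. It gives a reason, "As food restriction and severe weight loss are central to the psychopathology of AN", and then the exemption: "an intermittent inpatient treatment up to four weeks is not considered a Serious Adverse Event (SAE". The next sentence completes the definition: "All other fatal or life-threatening events are defined as SAE". No further criterion of seriousness is given.

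The same section sets two reporting routes. For serious events: "SAEs have to be reported immediately to the principal investigator and the central ethics committee". For the rest: "All adverse events are documented and reported to the principal investigator". It adds: "An Independent Safety Monitoring Board was implemented at the outset".

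Admissions are foreseen in two other places:

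- The Medical complications section has CBT and FPT patients hospitalized when BMI falls below 14. Outpatient treatment resumes if BMI reaches at least 14 within four weeks, and otherwise "if there is no improvement, the patient is withdrawn from the intervention treatment". It also provides more generally: "In the event of medical complications such as malnutrition or the manifestation of a severe psychiatric disorder, short-term hospitalization should be considered".
- The Discussion describes up to four weeks of inpatient crisis treatment as part of the protocol, either after a BMI drop below 14 or after medical complications.

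**The concern.** SAE status decides how fast an event is reported and to whom. Serious events go at once to the principal investigator and the central ethics committee. For other adverse events the article mentions neither speed nor the committee. A boundary that does not follow its own rationale can send events down the slower route for no stated reason.

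The stated reason concerns starvation and weight loss. The Abstract, however, attributes mortality in anorexia nervosa to suicide as well as malnutrition, and the Medical complications section expects psychiatric admissions. A rule justified by the first cause but worded for any cause may also take in the second.

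Admission is also an informative sign of deterioration in an outpatient trial. If SAE counts leave out many types of admission, they say little about whether admissions differ between arms.

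**Working it through.** The article gives no figure for this point, so there is none to reproduce and no arithmetic settles it. The check is to apply the rule as written to each kind of admission that the article foresees. Two readings of the exemption are possible: *narrow* (only stays for the stated weight-loss reason) and *broad* (any inpatient stay up to four weeks).

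1. **Up to four weeks, starvation or weight loss.** Not an SAE on either reading. This holds even when the starvation is life-threatening, because the word *other* in the residual clause sets these stays aside.
2. **Up to four weeks, another cause, not life-threatening** (for example a severe psychiatric disorder). Not an SAE on either reading. On the broad reading it is exempt. On the narrow reading it is not exempt but meets no remaining criterion.
3. **Up to four weeks, another cause, life-threatening** (for example a suicide attempt). An SAE on the narrow reading, unclear on the broad one.
4. **Beyond four weeks, any cause, not life-threatening.** The exemption no longer applies, but neither does any criterion. Not an SAE by the literal wording.
5. **Beyond four weeks, life-threatening or fatal.** An SAE.

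Three results follow.

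- **Missing criterion.** Case 2 comes out the same on both readings, so narrowing the exemption would not be enough by itself. The cause is that admission is absent from the criteria.
- **Four-week limit.** Comparing case 2 with case 4, and case 1 with case 4 where the starvation is not life-threatening, crossing four weeks changes nothing. The limit alters status only for life-threatening events, such as life-threatening starvation moving from case 1 to case 5. For all other admissions it does no work. A CBT or FPT patient who has not improved after four weeks and is withdrawn from the intervention, and whose stay continues, falls in case 4 unless the event is judged life-threatening.
- **Scope of the exemption.** Case 3 depends on which reading is meant. The opening clause supports the narrow one. The Discussion attaches the same four-week allowance to medical complications generally, which supports the broad one. The sections do not settle it.

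On size, the inputs would be the number, cause and length of admissions. None is given, so no count of affected patients can be calculated.

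**The case against.** The strongest reply is that the exemption is deliberate and reasoned. Starvation-related admission is an expected feature of this disease, and the Discussion explains that inpatient crisis treatment was built in so that patients with complications would not be dropped. The word *other* shows that the authors knew they were setting aside some life-threatening events. This stands: sparing expected weight-related stays from SAE status is a legitimate prespecified choice, not a contradiction.

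A second reply is that the context favours the narrow reading, and that a four-week limit would be pointless unless longer stays were meant to be treated differently. Both are fair inferences about intent. The text states neither, and case 2 fails even on the narrow reading.

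A third reply is that all adverse events are documented and a safety board exists. This also stands, and it limits the point: what is lost is classification and the immediate route, not recording. A reader might infer that admissions go unrecorded or would be left out of the final report. Nothing in the article shows that.

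Finally, the BMI-triggered admission rule is stated for CBT and FPT, whereas TAU patients are advised to see their GP monthly, with study staff arranging more intensive care if needed. Counting more admissions as SAEs could therefore add protocol-driven events to the intervention arms. This is a reason for care in reading the counts by arm. It is not a reason to leave the definition unclear.

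**Conclusion.** The point holds as a defect in how the SAE definition is fixed. Admission is not a criterion, the exemption is worded more widely than its reason, and stays beyond four weeks that are not life-threatening fall outside SAE status on the literal wording. Psychiatric admissions, admissions for other complications, and prolonged stays that lead to withdrawal can therefore miss immediate reporting to the ethics committee, though they remain documented adverse events.

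A reader might go further and infer that most admissions are never SAEs, or that the main harm signal of the trial is lost. The article does not support this. It gives no number or length of admissions and names no main harm signal. Deaths remain SAEs, and so do life-threatening events outside the exemption. Nor can a count be attached. An assumed admission rate of 10% to 20% would give 0.10 × 237 = 23.7 to 0.20 × 237 = 47.4, or about 24 to 47 patients. That rate has no basis in the article, and the result counts everyone admitted, including those whose event would still be an SAE.

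The conclusion rests on the literal wording of the published article. It is a cheap improvement to safety oversight and does not affect the efficacy analysis.

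**What to change.** Reconcile the Safety aspects and Medical complications sections and the matching paragraph of the Discussion:

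- limit the exemption expressly to expected weight-related inpatient stays of up to four weeks;
- classify other admissions, and any stay beyond four weeks, as SAEs alongside fatal and life-threatening events;
- tabulate every admission, exempt or not, by reason, duration and arm for the Independent Safety Monitoring Board and the final report, with a note that the BMI-triggered admission rule is stated for CBT and FPT only.

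The cost is one amended definition and one extra listing. More events will be labelled serious and reported immediately. Nothing here changes when patients are admitted, treated or withdrawn.
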